### Interim analysis

After the last patient is enrolled and all the baseline data including calcification status are collected, the data management committee will perform an interim analysis to evaluate all baseline data.

### Ethical considerations

This study will be conducted in accordance with the principles established by the 18th World Medical Assembly (Helsinki, 1964) and all subsequent amendments. The study was approved by institutional review boards of all participating centers and registered with the Chinese Clinical Trial Registry (ChiCTR-OCH-14004447 at http://www.chictr.org/en/). Written informed consent for participation in the study will be obtained from all participants. Ethical approvals are provided by all participating centers.

### Determination of sample size

From the latest published annual data, the mortality rate of Chinese CKD dialysis patients is approximately 10 %, so we assume the 2-year mortality rate for Chinese CKD dialysis patients is around 20 % [24]. Assuming the ratio between patients with and without VC is 7:3, a two-sided log rank test with an overall sample size of 1520 subjects (of which 1064 are in the VC group and 456 are in the non-VC group) achieves 80 % power at a 0.05 significance level to detect a difference of 0.07 between 0.79 and 0.86—the proportions surviving in VC groups and without VC group, respectively. This corresponds to a hazard ratio of 0.6398. The proportion of patients lost during follow-up is predicted to be 20 %. These results are based on the assumption that the hazard rates are proportional. Therefore, 1520 subjects are to be recruited.

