## Background

Chronic kidney disease (CKD) is a critical health problem. It is estimated that there were nearly 120 million patients with CKD in China with an overall prevalence of 10.8 % [1]. It is similar to that in the United States (13.1 %) and Norway (10.2 %) but the awareness of CKD (10.04 %) is still relatively low in China [2–4]. The number of patients with end-stage renal disease (ESRD) is estimated to be 2 million in China, but less than 20 % of patients are undergoing dialysis [5].

Vascular calcification (VC) is a common complication associated with CKD and the major cause of cardiovascular disease (CVD) in patients with ESRD [6]. In contrast, patients without VC always have a better prognosis with limited progression of VC over a longer period of time [7]. The prevalence of VC increases as CKD progresses, from 40 % at stage 3 CKD to 80–99 % at stage 5 CKD on dialysis (CKD stage 5D) [8–12].

Mineral and bone disorder (MBD) is also a frequent complication of CKD associated with increased risk of VC, arterial dysfunction, morbidity and mortality [13]. A meta-analysis revealed that every 1.0 mg/dL of serum phosphorus was associated with 18 % increase of the risk of death in patients with CKD, indicating that hyperphosphatemia is an independent risk factor for mortality among those patients [14]. Hyperphosphatemia is increasingly considered the cause and a key factor inducing early and progressive VC in patients with CKD, implying that vigorous treatment of hyperphosphatemia with phosphate binders is essential to the prevention of VC [15, 16]. In addition, hyperphosphatemia is a key regulator involved in multiple mechanisms that induce and promote the progression of VC [15]. Therefore, prevention of MBD and lowering the circulating levels of phosphate and calcium have become major targets in the treatment of VC [17].

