## Discussion

VC is a major contributor to CVD, which is a significant cause of mortality in ESRD. However, the burden and management of VC in Chinese patients with CKD on dialysis are still unknown. Given that clinical trials are considered the best way to provide evidence and related knowledge for guidance, it is necessary to design a high quality national observational study that is capable of addressing these issues.

The CDCS is a uniquely-designed observational cohort study seeking to collect detailed clinical, biochemical and laboratory data to inform the prevalence and impact of management of VC in Chinese patients with CKD on dialysis, and test the hypothesis that baseline VC is a predictor for all-cause/CVD mortality and non-fatal CV events. This study aimed to recruit well-characterized patients in order to avoid incidence-prevalence bias, and the sample size will be large enough to achieve multiple study objectives with adequate variability [25].

This study may be limited by the nature of the design as an observational study, in comparison with randomized controlled trials which can commonly provide stronger evidence in the efficacy of therapies. Since the proportion of patients receiving HD or PD cannot be predefined, the strength of comparing the outcome between the two groups may be weakened. In addition, collection of some prognostic factors (e.g., brain natriuretic peptide and troponin) for CVD was not included in the study design as these tests will not be applicable for every enrolled patient in the real-world clinical practice setting.

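### The 80 % power for the key survival comparison rests on an unexplained 7:3 VC split that lies below the 80–99 % prevalence given in the Background; over most of that range the power is well short of 80 %.

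*Protocol article*

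**What the plan says.** The section Determination of sample size describes "a two-sided log rank test with an overall sample size of 1520 subjects". The groups are then given in brackets: "of which 1064 are in the VC group and 456 are in the non-VC group". The design, it says, "achieves 80 % power at a 0.05 significance level". The effect on which this rests is worded "to detect a difference of 0.07 between 0.79 and 0.86", meaning survival with and without VC in that order. The section gives a hazard ratio of 0.6398 and expects 20 % of patients to be lost. The group sizes come from one planning statement: "Assuming the ratio between patients with and without VC is 7:3". No source or sensitivity range is attached to it.

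The Background, citing earlier studies, says VC prevalence rises with CKD stage to "80–99 % at stage 5 CKD on dialysis". That is the disease stage enrolled here.

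Under Secondary analysis, all-cause survival with versus without VC is the key secondary analysis. Patients without VC are also the reference group for the separate coronary, abdominal aortic and valve comparisons. The Discussion states that "the sample size will be large enough to achieve multiple study objectives with adequate variability".

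**The concern.** The power of a two-group survival comparison depends heavily on the smaller group. The plan counts on 456 patients free of VC. At 80–99 % VC, 1520 patients would contain only 304 down to about 15. The 7:3 split is therefore not a cautious value within the document's range; it lies outside that range on the favourable side.

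The way VC is used points the same way. Each of the three site-specific comparisons is made against patients without VC, so VC reads as calcification at any of the three sites. A combined definition can only be as common as, or more common than, its commonest component.

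This comparison is the only stated basis for the 1520. If the VC-free group turns out small, a non-significant result could be taken as adequately powered evidence that VC does not predict death, when the test had little chance of showing it. The site-specific and cardiovascular-mortality comparisons use the same reference group.

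**Working it through.** **Inputs.** From Determination of sample size: N = 1520, two-sided α = 0.05, two-year survival 0.79 (VC) and 0.86 (no VC), loss 20 %, VC share p = 0.70. From the Background: p = 0.80 to 0.99.

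**Hazard ratio.** ln 0.86 / ln 0.79 = 0.6398 (no VC versus VC), as stated. The inverse is h = 1.5629.

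**Reproducing the plan.** Patients after loss: 0.8 × 1520 = 1216. Expected deaths: d = 1216 × [0.21p + 0.14(1 − p)]. With φ = p/(1 − p), Freedman's formula is

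power = Φ( √(dφ) × (h − 1)/(1 + φh) − 1.960 ).

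At p = 0.70: φ = 2.333 and d = 1216 × 0.189 = 229.8. Then √(229.8 × 2.333) × 0.5629/4.647 = 2.805, and Φ(0.845) = 80.1 %. The same formula solved for N needs 229.2 deaths, and 229.2/0.189/0.8 is about 1516, against the stated 1520. The stated figure is reproduced.

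**Changing only the split.**
- p = 0.80: φ = 4, d = 1216 × 0.196 = 238.3; √(238.3 × 4) × 0.5629/7.252 = 2.397; Φ(0.437) = 66.9 %.
- p = 0.90: φ = 9, d = 1216 × 0.203 = 246.8; √(246.8 × 9) × 0.5629/15.066 = 1.761; Φ(−0.199) = 42.1 %.

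Schoenfeld's formula, Φ( √(d p(1 − p)) × ln h − 1.960 ), uses the same deaths. Deaths without VC are 1216 × (1 − p) × 0.14.

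| VC share | VC / no VC | Deaths | Deaths without VC | Freedman | Schoenfeld |
|---|---|---|---|---|---|
| 70 % | 1064 / 456 | 229.8 | 51.1 | 80.1 % | 87.3 % |
| 80 % | 1216 / 304 | 238.3 | 34.0 | 66.9 % | 78.7 % |
| 85 % | 1292 / 228 | 242.6 | 25.5 | 56.3 % | 70.0 % |
| 90 % | 1368 / 152 | 246.8 | 17.0 | 42.1 % | 55.8 % |
| 95 % | 1444 / 76 | 251.1 | 8.5 | 24.4 % | 33.8 % |
| 99 % | 1505 / 15 | 254.5 | 1.7 | 8.3 % | 10.5 % |

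**Other methods.** A two-proportion test with 20 % loss gives 83.1 % at 70 % VC, 70.9 % at 80 %, 43.7 % at 90 % and 5.5 % at 99 %. Of the variants tried at 7:3, only Freedman with 20 % loss comes within two points of 80 %, so it is the like-for-like comparison. If overall two-year mortality is held at 20 % instead of the group survivals, Schoenfeld with 20 % loss gives 89, 80, 55 and 10 % at 70, 80, 90 and 99 % VC, almost the same pattern.

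**Detectable hazard ratio at 80 % power.** Hold VC survival at 0.79, set survival without VC to 0.79^HR, recompute d, and solve for HR. Check at 90 % VC with HR 0.433: survival without VC is 0.903, d = 1216 × (0.189 + 0.0097) = 241.6 and h = 2.31. Then √(241.6 × 9) × 1.31/21.8 = 2.80 = 1.960 + 0.842, as required.

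| VC share | Freedman | Schoenfeld |
|---|---|---|
| 70 % | 0.64 | 0.67 |
| 80 % | 0.58 | 0.64 |
| 90 % | 0.43 | 0.55 |
| 95 % | 0.21 | 0.44 |

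**Scale.** For 80 % power at the planned effect, Freedman would need about 2077 patients at 80 % VC and about 3850 at 90 %.

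**The case against.** **The calculation is right.** At its stated inputs it is. A reader might infer an arithmetic error, but 80 %, 1520 and 0.6398 all reproduce. The fault is a planning assumption that conflicts with another statement in the same document.

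**Chinese prevalence is unknown.** The article says so, and the 80–99 % comes from cited studies that it does not describe as Chinese. The eligibility criteria also exclude amputation, severe peripheral vascular lesions and arrhythmia, which could lower VC prevalence. So it would go too far to say that prevalence in this cohort is shown to be 80 % or more. What remains is that uncertainty calls for a range or a reason, and the plan gives one value outside the only figures it cites.

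**The size depends on the formula.** This stands at the lower end. Schoenfeld gives 79 % at 80 % VC. Simulated log-rank tests (2000 runs, loss at entry or spread over follow-up) give 84–88 % at 70 % VC, 72–74 % at 80 % and 43–49 % at 90 %, so Freedman is somewhat conservative. Calling the test underpowered as soon as VC reaches 80 % would be too strong. At 90 % and above every method falls clearly short.

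**It is a secondary analysis.** True. The primary objective is prevalence, where 1520 patients give a 95 % half-width of 1.96 × √(0.7 × 0.3/1520) = 2.3 points at 70 % VC, and less at higher prevalence. But the survival comparison is named as the key secondary analysis, and it is what the sample size was built on.

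**Conclusion.** The point holds as a conflict between the sample-size assumption and the Background, not as a calculation error. On the plan's own survival proportions, loss and formula, power is about 67 % at the bottom of the 80–99 % range, 42 % at 90 % and 8 % at 99 %. With Schoenfeld it is 79, 56 and 11 %. The claim of 80 % therefore does not hold over most of the document's own range. At 80 % VC the shortfall is modest and depends on the method; from about 85–90 % it is clear. This assumes group survivals of 0.79 and 0.86 whatever the split, proportional hazards, and 20 % of patients contributing no events.

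Two further inferences are tempting and are not supported. One is that deaths will fall below plan, because "the mortality rate of Chinese CKD dialysis patients is approximately 10" % a year describes dialysis patients in general while the cohort excludes sicker patients. The documents give no mortality figure for the selected cohort, so neither a size nor a firm direction can be stated. The other is that formal inference should move to graded severity. Severity is in the stated hypothesis, but that would change the key test, and no power calculation for it is available.

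**What to change.** 1. In Determination of sample size, either justify 7:3 against the Background range, or replace the single power statement by power and detectable hazard ratio at 70, 80, 90 and 95 % VC, naming the formula. With Freedman and 20 % loss the powers are 80, 67, 42 and 24 %.
2. State that these figures will be recomputed with the observed VC split at the baseline-data analysis already planned under Interim analysis, before outcomes are analysed.
3. State that if VC is about 85–90 % or more, a null result for VC versus no VC is not adequately powered evidence of no association. Qualify the Discussion's sample-size claim to match.

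The cost is rewording and a less favourable stated power. No extra patients, visits or change of test are needed.

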## Discussion

VC is a major contributor to CVD, which is a significant cause of mortality in ESRD. However, the burden and management of VC in Chinese patients with CKD on dialysis are still unknown. Given that clinical trials are considered the best way to provide evidence and related knowledge for guidance, it is necessary to design a high quality national observational study that is capable of addressing these issues.

The CDCS is a uniquely-designed observational cohort study seeking to collect detailed clinical, biochemical and laboratory data to inform the prevalence and impact of management of VC in Chinese patients with CKD on dialysis, and test the hypothesis that baseline VC is a predictor for all-cause/CVD mortality and non-fatal CV events. This study aimed to recruit well-characterized patients in order to avoid incidence-prevalence bias, and the sample size will be large enough to achieve multiple study objectives with adequate variability [25].

This study may be limited by the nature of the design as an observational study, in comparison with randomized controlled trials which can commonly provide stronger evidence in the efficacy of therapies. Since the proportion of patients receiving HD or PD cannot be predefined, the strength of comparing the outcome between the two groups may be weakened. In addition, collection of some prognostic factors (e.g., brain natriuretic peptide and troponin) for CVD was not included in the study design as these tests will not be applicable for every enrolled patient in the real-world clinical practice setting.

In conclusion, as the first large-scale Chinese cohort study of patients with CKD on dialysis, the CDCS will utilize unique data for VC prevalence, demographic characteristics and disease management of the Chinese dialysis population to supplement the limitation of currently available data. The new results gained from the CDCS will provide increasing awareness of the importance of calcium balance and the risks of calcification, enable better clinical decisions and outcomes in assessing VC and management of serum phosphorus, calcium and iPTH in Chinese CKD patients on dialysis for nephrologists and health care providers, and be supportive for new clinical trials among Chinese CKD patients in the future. Further analysis of this cohort and comparison with other cohort studies in western countries might provide useful insight regarding race discrepancies on VC and related disease management in CKD patients.

### Trial status

This trial is still recruiting on the day of submission.

## Abbreviations

CKD: Chronic kidney disease
ESRD: End-stage renal disease
VC: Vascular calcification
CVD: Cardiovascular disease
CKD stage 5D: Stage 5 CKD on dialysis
MBD: Mineral and bone disorder
CDCS: China Dialysis Calcification Study
HD: Hemodialysis
PD: Peritoneal dialysis
KDGIO: Kidney Disease: Improving Global Outcomes
iPTH: Intact parathyroid hormone
FGF23: Fibroblast growth factor 23
CCI: Cardiovascular calcification index
BMI: Body mass index
25-OH Vit D: Serum 25-hydroxyvitamin D
K/DOQI: Kidney Disease Outcomes Quality Initiative
CAC: Coronary artery calcification
AAC: Abdominal aortic calcification
EBCT: Electron beam computed tomography
MDCT: Multi-detector computed tomography
LVMI: Left ventricular mass index
LVH: Left ventricular hypertrophy
HU: Hounsfield units
CIs: Confidence intervals
ABI: Ankle-brachial index
ROC curve: Receiver operating characteristic curve
AUC: Area under the curve
